## INTRODUCTION

Since the early 1980s, the standard approach to immunosuppression in transplant recipients has involved the use of calcineurin inhibitors (CNI) such as cyclosporine (CsA) and tacrolimus. CNIs reduce the number of acute rejection episodes and enhance short-term allograft survival. However, the greater benefit appears to be a decrease in the number of acute rejections during the first months after transplantation. Progressive chronic nephrotoxicity is a major toxic effect of CNI in the long term and is associated with mild-to-moderate renal dysfunction. Death from cancer or cardiovascular diseases with a functioning graft is also a major cause of late graft loss. The balance between preventing immunological allograft failures, avoiding over immunosuppression and managing nephrotoxicity is therefore still an unresolved issue. The introduction of immunosuppressive drugs such as mycophenolate mofetil (MMF) and sirolimus (SRL) has strengthened the case for minimizing the use of CsA. SRL is an antifungal macrolide that displays potent antiproliferative activities that produce immunosuppressive effects. Binding of SRL to the intracellular immunophilin FKBP12 blocks the activity of the mammalian target of rapamycin (mTOR) with potent inhibition of downstream signal ligand progression from the G1 to the S phase of the cell-cycle. SRL has been shown to reduce the incidence of acute rejection after renal transplantation, without appearing to cause significant inherent nephrotoxicity in most animal and human studies. However, when combined with CNI therapy, renal function often worsens as a result of potentiated nephrotoxicity. SRL has therefore been used as a primary immunosuppressant in CNI-free regimens. Together with anti-CD25 antibody or anti-thymocyte globulins, MMF and steroids, these regimens have provided comparable 1-year patient and graft survival, and incidence of acute rejection episodes. Furthermore, renal function was also significantly better in the CsA-free group and did not tend to worsen during the first year after transplantation. However, early use of SRL after transplantation has been demonstrated to be associated with various complications including lymphocele, prolonged delayed graft function (DGF), delayed wound healing and by a slight increased incidence of acute rejection. This study could help in evaluating the ideal dose, trough blood level, safety and benefits of conversion to Sirolimus based regimen from CNI based regimen in Indian patients.

## REVIEW OF LITERATURE

During the past decade there has been a major shift in the focus of kidney transplant research from the prevention of acute rejection to the recognition and targeting of risk factors that associate with late graft loss beyond 1 year. It is now apparent that the major causes of kidney graft loss beyond 1 year after transplantation are progressive deterioration of graft function, often termed chronic allograft nephropathy (CAN), the hallmark of which is histological evidence of tubular atrophy, interstitial fibrosis, and transplant glomerulopathy; and patient death from cardiovascular disease, often with a functioning kidney graft. What has also emerged is that many of the same risk factors associated with the former are also associated with the latter. These include age, diabetes, both preexisting and occurring after the transplantation, poorly controlled hypertension, dyslipidemia, viral infections, and diminished allograft function. In fact, renal dysfunction (estimated glomerular filtration rate (eGFR) <40 cc/min) itself appears to be an independent risk factor for coronary heart disease and death.

A cruel irony that has accompanied the control of acute rejection via the widespread introduction of CNI drugs nearly 30 years ago has been their direct and indirect toxicity to the kidney. CNI nephrotoxicity appears to target the renal microcirculation by promoting preglomerular vasoconstriction, as well as direct injury resulting in hyalinosis of blood vessels. In addition, CNIs appear to favor the progression of post-transplantation hypertension, hyperglycemia, dyslipidemia, and oncogenesis, which are associated with late morbidity. Although variable in severity and often dose related, CNI nephrotoxicity contributes to the decline in kidney function over time. The pattern of injury is perhaps best chronicled in non-transplant patients treated for autoimmune disease who lost 50% of their native renal function and developed histological striped fibrosis after 2 years of continuous CNI use.

For these reasons, CNI dose reduction, elimination, or avoidance has become the focus of numerous clinical kidney transplant trials with measurements of renal function rather than acute rejection as the primary efficacy end point.

In fact, initial experiences of CNI avoidance in a single-arm study with MMF, daclizumab and steroids resulted in unacceptably high acute rejection rates, though with good renal

function and patient and graft survival. SRL, a potent macrolide immunosuppressant claimed as a non-nephrotoxic drug, was initially tested in clinical trials in association with CNIs. This combination greatly reduced acute rejection rates, but resulted in increased nephrotoxicity. Thus, the CNIs-SRL combination is not so far the ideal immunosuppression for avoiding nephrotoxicity in renal transplantation.

Some clinical investigators combined SRL with MMF in completely CNI-free protocols and it has been demonstrated by comparison of 2-year kidney biopsies that recipients treated with mycophenolate mofetil (MMF) and steroids and the mTOR inhibitor sirolimus in lieu of a CNI drug had diminished scarring and gene expression for fibrosis and tissue remodeling.

### Synergistic action of MMF and SRL in prevention of chronic allograft damage

MMF is a reversible inhibitor of inosine monophosphate dehydrogenase (IMPDH), blocking proliferation of lymphocyte; and SRL blocks cell proliferation induced by growth factors and cytokines by inhibiting the signaling protein mTOR (mammalian target of rapamycin). Furthermore, it has been described that the use of MMF in conjunction with SRL reverses its effect on transforming growth factor- $\beta$  production without apparent nephrotoxicity. All these facts suggest that the association of these two drugs may be useful in the design of non-nephrotoxic immunosuppressive regimens, and potent enough to keep down the acute rejection rate (Figure 1).

[figure not shown]

**Figure 1: Synergistic action of MMF and SRL**

In graft vasculopathy, abnormal vascular SMC proliferation and migration play major roles. In normal vessels, most SMC reside in the media, in which they are quiescent and possess a contractile phenotype characterized by the abundance of actin- and myosin-containing filaments. In disease states, SMCs re-enter the cell cycle, proliferate and migrate from the media to the intima. SRL inhibits both human and rat SMC proliferation by blocking cell-cycle progression at the G1/S transition and blocks rat, porcine and human SMC migration. In a nonhuman primate model of allograft vascular disease, the delayed introduction of SRL, to allow the development of vascular disease, halted the progression of pre-existing intimal thickening and was also associated with partial regression. The size of the allograft intimal area correlated inversely with SRL trough levels. In the same model, treatment with SRL from the day of transplantation prevented graft vascular disease. MMF was also studied for the prevention of allograft vascular disease in a similar experimental model. Although in this study there was no overall statistically significant difference in progression of graft vascular disease between the untreated and MMF-treated animals, there was close correlation between the total daily MMF dose and intimal hyperplasia. Depending on the individual tolerability of MMF in cynomolgus monkeys, MMF was effective for treatment of advanced graft vasculopathy after aortic transplantation. This efficacy was achieved when intimal proliferation had already proceeded unhindered for more than 6 weeks after transplantation due to lack of any immunosuppression. In a previous study in rodents, MMF and SRL more effectively inhibited intimal thickening than either drug alone, suggesting that the combined therapy of MMF and SRL may be effective for controlling graft vasculopathy in nonhuman primates or patients. In a classic model of chronic allograft rejection in rats, the effects of these two immunosuppressants were evaluated in a Lewis-to-Fisher donor/recipient strain combination. Rats treated with MMF or SRL alone showed a Banff sum score similar to the allograft control group. When the recipient rats were treated with MMF and SRL in combination, there was a statistically significant reduction of Banff sum score, with specific inhibition of vascular fibrous intimal thickening, allograft glomerulopathy and interstitial fibrosis. All these experimental studies suggest that the combination of MMF and SRL might be relevant to the prevention of acute rejection and CAN, especially graft vasculopathy.

### **Acute rejection prophylaxis: non CNIs based regimens**

#### ***De novo CNIs avoidance***

In a trial comparing corticosteroids, SRL and MMF versus corticosteroids, CsA and MMF, the incidence of biopsy-proven acute rejection at 12 months was not statistically significant

(27.5% in SRL and 18.4% in CsA), but in this study nearly 50% of patients treated with SRL and MMF received bolus steroids. They found a great number of adverse events in the SRL group, especially diarrhea, thrombocytopenia, hypercholesterolemia, hypertriglyceridemia and infectious pneumonia. However, dose of SRL and MMF dose was much higher than those now recommended. Indeed, target trough levels of SRL were 30 ng/mL for 2 months and 15 ng/mL thereafter, and MMF was given at 2 g a day. In an attempt to improve efficacy, Flechner et al. added induction therapy with basiliximab. The 2-year graft survival was greater than 90%, and the incidence of biopsy-proven acute rejection was 6.5% in SRL and 16.6% in CsA. Similar results were found when polyclonal antilymphocyte antibodies were used as induction therapy. In a randomized study of 132 living-donor renal recipients, Hamdy et al. compared SRL with low-dose TAC versus SRL-MMF in patients all receiving basiliximab and steroids. Incidence of acute rejection was 18.5% in SRL-TAC versus 13.5% in SRL-MMF.

The efficacy of the SRL and MMF combination for the prevention of acute rejection in a steroid-free protocol was also tested using Alemtuzumab induction therapy. In this study, the incidence of acute rejection was 36.3%.

The de novo use of lower-dose SRL (trough target range, 4–8 mg/ml) in combination with MMF has resulted in an increased risk of acute rejection, treatment failure, and reduced allograft survival compared with MMF/ tacrolimus and the use of SRL in early post surgical period has been variably associated with problems of wound healing.

### ***Switch to SRL in maintenance phase***

In recently published CONCEPT study, patients were converted to SRL at 3 months or maintained on cyclosporine, both in combination with MMF. In this study, patient and graft survival were not significantly different, but patients on the SRL regimen had improved renal function at the end of 1 year. The CONVERT trial findings indicated that improved graft function occurs in patients with eGFRs above 40 ml/min and a urine protein:creatinine ratio < 0.1 when they are randomly switched from CNIs to SRL 6 to 120 months post transplant period. In recently published Spare the Nephron trial, random switch over to SRL from CNIs 30 to 180 days post transplant resulted in similar measures of renal function but with fewer deaths and a trend to less Biopsy proven acute rejection and graft loss over 2 years of study period.

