## **MATERIAL AND METHODS**

### **PATIENTS**

Total number of patients to be studied will be 60.

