### **INCLUSION CRITERIA**

- Willing to sign informed consent
- Adult renal transplant recipients of either sex over the age of 18 years
- Undergone denovo live donor renal transplantation at least 2 months prior to enrolment
- Receiving CNI based maintenance regimen after transplantation
- Serum creatinine  $\leq 1.2$ mg/dl and proteinuria  $< 800$ mg/day

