FoxP3+ T regulatory cell population will be analyzed at baseline, and at 1, 3 and 6 months after enrolment. By flowcytometry using anti-human allophycocyanin (APC) conjugated-CD4 antibodies, phycoerythrin (PE)-Cy7 conjugated-CD25 antibodies (BD Biosciences) and Alexa-fluor 488 conjugated-FoxP3 antibodies (BD Biosciences) on BD FACS Aria II (BD Biosciences). A total of 20000 events will be acquired, and CD25+ FoxP3+T cells will be counted using FACS DIVA 6.0.

1: 1 randomization will be done with the help of a computer generated random number table, and allocation concealment will be achieved by opaque sequentially numbered sealed envelopes. The response of the patient to the therapy will be in terms of renal function assessment. The primary analysis will be two-sided independent sample t-test for difference of means for GFR estimation by MDRD method.

A sample size of at least 25 patients per treatment arm will provide at least 80% power based on the assumption of an effect size (difference of GFR estimates between two treatment arms) of 8 mL/min and S.D. as 10 mL/min

The secondary endpoints will be:

- Acute rejection
- Patient and graft survival at 6 months,
- Incidences of hyperlipidemia, NODM, hypertension and infectious complications
- Regulatory T-cell population

All patients will be followed up at 15, 30, 60, 120 and 180 days. All investigations required to determine the primary and secondary end points will be performed. Sirolimus levels will be determined at 5, 12, 30, 60 and 120 days in patients randomized to sirolimus arm whereas those on tacrolimus will have measurements at 30, 60 and 120 days.

The target trough levels are as follows:

- Sirolimus: 8-15ng/ml
- Tacrolimus: 8-10 ng/ml upto mo 3, 6-8 ng/ml thereafter
- Cyclosporine: 200-300 ng/ml upto mo 3, 150-250 ng/ml thereafter

All unexplained episodes of graft dysfunction will be investigated by biopsy. Acute rejection will be treated as per standard protocol.

Variables will be presented as mean  $\pm$  SD and categorical variables as percentages. Appropriate statistical studies will be used for analysis of results. Two-tailed P-value  $<0.05$  will be considered significant.

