| Vital Parameters
(PR, BP, Fluid Intake and Urine output)                                                                                                                                      | X        | X                   | X                   | X               | X                | X                |
| Blood tests
CBC, Serum creatinine, Blood urea, electrolytes, Blood sugar, lipid profile, SGOT, SGPT, Urine for routine analysis, 24hrs urine for protein and Urine protein to creatinine ratio | X        | -----               | -----               | -----           | X                | X                |
| Therapeutic drug monitoring                                                                                                                                                                       |          |                     |                     |                 |                  |                  |
| i. Rapacan group                                                                                                                                                                                  | ----     | X                   | X                   | X               | X                | X                |
| ii. CNI Group                                                                                                                                                                                     | ----     | -----               | -----               | X               | X                | X                |
| Dose titration of                                                                                                                                                                                 |          |                     |                     |                 |                  |                  |
| i. Rapacan                                                                                                                                                                                        |          | X                   | X                   | X               | X                | X                |

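### The primary GFR comparison ignores baseline proteinuria, although the protocol's own conversion evidence singles out low-proteinuria patients and eligibility is much wider; adjust for it and say which patients the 8 mL/min describes

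*Protocol*

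**What the plan says.** The Protocol's section on switching to sirolimus in the maintenance phase describes three conversion trials. For the one that converted patients 6 to 120 months after transplant, it reports that "improved graft function occurs in patients with eGFRs above 40 ml/min and a urine protein:creatinine ratio < 0.1". This is the only one of the three for which a renal-function or proteinuria condition is given. The trial converting at 3 months is described as showing better renal function at 1 year, and the trial converting at 30 to 180 days as showing similar renal function.

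The Inclusion Criteria require serum creatinine of at most 1.2 mg/dl and "proteinuria $< 800$ mg/day".

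Study Method places the baseline tests, including 24-hour urine protein, before randomisation. The Study Visit Plan lists "24hrs urine for protein and Urine protein to creatinine ratio" at visit 0. On allocation, Study Method says "1: 1 randomization will be done with the help of a computer generated random number table" and names no stratification factor. It fixes the primary analysis as a two-sided independent-sample t-test on MDRD GFR, which has no covariate.

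On size, "A sample size of at least 25 patients per treatment arm will provide at least 80% power", assuming an "effect size (difference of GFR estimates between two treatment arms) of 8 mL/min and S.D. as 10 mL/min". No source or patient group is given for the 8 mL/min. The Patients section sets the total: "Total number of patients to be studied will be 60".

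**The concern.** The creatinine limit broadly follows the renal-function half of the cited profile. The proteinuria limit does not follow the other half, and no reason is given. Patients well above the cited ratio can therefore enter, and the primary comparison averages over them without using a value already in hand.

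Two things are at stake. First, if conversion helps less at higher proteinuria, the average difference in the admitted population is below 8 mL/min and the trial is smaller than it should be. Second, if proteinuria predicts later GFR, leaving it out of the analysis wastes precision and lets a chance imbalance blur the estimate. The protocol itself fixes the primary test, so an adjusted primary analysis introduced elsewhere would conflict with it.

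**Working it through.** **Inputs from the Protocol.** Difference 8 mL/min, SD 10 mL/min, two-sided 5% ("Two-tailed P-value $<0.05$ will be considered significant"), 25 per arm planned, 60 in total (30 per arm).

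**Inputs assumed, because the documents do not give them.** The share *p* of patients with a ratio of 0.1 or more; the effect *e* in those patients; a mg/mg ratio; creatinine excretion of 1.0 to 1.5 g/day.

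**Step 1: reproduce the stated size.** n = 2(1.960 + 0.842)² × 10² / 8² = 24.5, so 25 per arm, as stated. The t distribution gives 79% power at 25 per arm, needs 26 for 80%, and gives 86% at 30.

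**Step 2: how much wider is the eligibility limit?** A ratio of 0.1 corresponds to 0.1 × 1000 = 100 mg/day up to 0.1 × 1500 = 150 mg/day. Then 800/150 = 5.3 and 800/100 = 8.0.

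**Step 3: average effect and power.** Average effect = 8(1 − p) + e·p. Power is from the noncentral t with SD 10.

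| Effect *e* at ratio ≥ 0.1 | *p* | Average effect (mL/min) | Power, 30 per arm | Power, 25 per arm | n per arm for 80% |
|---|---|---|---|---|---|
| 8 (equal) | any | 8.0 | 86% | 79% | 26 |
| 4 (half) | 30% | 6.8 | 74% | 65% | 35 |
| 4 (half) | 50% | 6.0 | 63% | 55% | 45 |
| 0 (none) | 10% | 7.2 | 78% | 70% | 32 |
| 0 (none) | 30% | 5.6 | 57% | 49% | 52 |
| 0 (none) | 50% | 4.0 | 33% | 28% | 100 |

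Allowing for the extra spread that a mixed effect creates in the sirolimus arm lowers the 30-per-arm figures for *e* = 0 slightly, to 54% at p = 30% and 31% at p = 50%. With *e* = 0, 30 per arm keeps 80% power only if about 92% or more of patients are below 0.1.

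**Step 4: chance imbalance without stratification.** Taking two independent binomials of 30, the arms differ by 5 or more high-ratio patients in 20% of trials at p = 30%, 24% at 40% and 25% at 50%. If proteinuria carried a 5 mL/min difference in GFR (assumed), a 5-patient gap would shift the comparison by 5 × 5/30 = 0.8 mL/min. The standard error is 10√(2/30) = 2.6 mL/min. In 40,000 simulated trials per scenario (p = 30%, prognostic difference 0 to 10 mL/min), the unadjusted t-test rejected a true null in 4.8% to 5.1%.

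**Step 5: what adjustment gains.** With the same assumed 5 mL/min difference, the residual SD is √(100 − 25·p(1 − p)). At p = 30% this is √94.75 = 9.73. Power for a true 8 mL/min at 30 per arm rises from 86% to about 88%.

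**Step 6: what subgroup estimates can show.** At p = 30% there are 9 high-ratio patients per arm. The 95% CI half-width in them is 2.12 × 10√(2/9) = 10 mL/min. For an interaction of the full 8 mL/min, the standard error is 10√(2/9 + 2/21) = 5.6 mL/min and power is 29%. Over p = 20% to 50%, power is 23% to 33%.

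**The case against.** A reader might infer that proteinuria is an established modifier of the sirolimus effect and that this trial's GFR effect is therefore diluted. The documents do not support that. The literature review reports a subgroup with benefit, defined jointly by eGFR and ratio. It reports no interaction and does not say that benefit is absent at 0.1 or above. The other two conversion trials are described without a proteinuria limit, and their windows (3 months; 30 to 180 days) also bear on a trial that enrols from 2 months. Dilution relative to plan further requires that the 8 mL/min describes low-proteinuria patients, which the protocol does not say. All of this stands, and it makes the lower rows of the power table conditional.

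A reader might also infer that chance imbalance biases the randomised test. It does not: type I error is held, and Step 4's shift is small against the standard error.

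It can be argued too that the remedy does not cure the harm. Adding a main effect leaves the average effect where it was, and subgroup estimates are too imprecise to tell a failed conversion from an unsuitable case mix. That is correct and limits what the fix may claim. Finally, choosing a stratification factor in 60 patients is discretionary, and subgroup reporting is commonly left to an SAP. That also stands. It does not reach the primary test, which the protocol itself fixes without a covariate.

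**Conclusion.** The point holds in a limited form. The protocol cites evidence of benefit at low proteinuria, admits a range about 5 to 8 times wider (under the stated unit and excretion assumptions), measures proteinuria at baseline and makes no use of it in the primary comparison. It also leaves unsaid which patients the 8 mL/min describes.

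The possible loss of power runs from none (86% at 30 per arm) to severe (33%), depending on two quantities that the documents do not give. It is a risk to be addressed in the sample-size justification, not a demonstrated defect. What can be secured with confidence is smaller: protection of the estimate against chance imbalance, and a modest precision gain, about 86% to 88% power if proteinuria carries a 5 mL/min difference.

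**What to change.** In Study Method, replace the unadjusted t-test with a pre-specified linear model of 6-month MDRD GFR on treatment, adjusted for baseline proteinuria or protein:creatinine ratio, preferably as a continuous term, alongside baseline GFR. Report the sirolimus-minus-CNI difference with its 95% CI overall and, labelled supportive only, below and at or above a ratio of 0.1. State the source of the 8 mL/min and the population it describes; if it applies only to low-proteinuria patients, show power over a plausible range for the rest.

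Stratified allocation is optional. If chosen, it needs blocks within strata, since separate simple lists would balance nothing; if enrolment has begun, keep the list and change only the analysis.

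The sponsor should reconcile the proteinuria limit with the cited evidence, or explain the difference. No threshold is proposed here.

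The cost is two model terms and a few sentences, with no new test, visit or patient. The limits should be stated: adjustment does not restore power lost to a smaller average effect, and the subgroup intervals will be wide.
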